### Number of patients and eligibility criteria

There will be a maximum of 24 patients in the MTD evaluation part of phase I: 12 patients for CLL / low-grade NHL, 12 patients for high-grade NHL. There will be a maximum of 12 patients in phase II of the study: 6 patients for CLL / low-grade NHL, 6 patients for HG-NHL. A total of maximal 30 patients will be included in the study.

Patients of both genders, any ethnic origin and at least 18 years old are included in the study if they meet the criteria given in Table 2. All participating patients have to sign the written informed consent. Patients can be withdrawn from the study for medical reasons at any time and must be withdrawn in the event of a dose-limiting toxicity. Patients can recall their consent at any time without any negative implications for their further treatment.

**Table 2 T2:** Eligibility criteria of the FBTA05 trial

	
**Inclusion criteria**	- confirmed CLL, low-grade NHL or high-grade NHL
	- CD20 positivity
	- relapsed or refractory disease > 60 days after allogeneic transplantation
	- adequate hematological, liver and kidney functions
	- platelet count ≥ 25 G/l
	- ECOG performance status ≤ 2
	- negative pregnancy test (adequate contraception during study in women of child bearing potential)
**Exclusion criteria**	- anti-CD20 or anti-T cell antibody treatment < 3 months before FBTA05 treatment
	- positivity for human anti-mouse antibodies
	- history of GVHD °III or °IV, or GVHD requiring steroid therapy with ≥ 10 mg / day
	- known hypersensitivity to recombinant murine or rat proteins
	- acute or uncontrolled chronic infections, viral infections at risk of reactivation (e.g. HCV, HBV, HIV)
	- patients unable or unwilling to comply fully with the protocol

*CLL* chronic lymphocytic leukemia, *NHL* Non-Hodgkin's lymphoma, *ECOG* Eastern Cooperative Oncology Group, *HAMA* human anti-mouse antibody, *GVHD* graft versus host disease, *HCV* hepatitis C virus, *HBV* hepatitis B virus, *HIV* human immunodeficiency virus.

### Drug formulation

The investigational drug FBTA05 is provided by the TRION Pharma GmbH (Munich, Germany) as a sterile, pyrogen-free, color-free and preservative-free solution for infusion. The concentrate contains 0.2 mg/ml antibody per 100mM sodium citrate buffer (pH 5.6), with 0.02% Tween 80. Depending on the dose level, FBTA05 is further diluted in 0.9% sodium chloride solution for i.v. infusion.

### Study treatment

FBTA05 is administered with a constant rate over 6 hours by intravenous (i.v.) infusion. To avoid infusion reactions typically occurring after i.v. antibody infusions, i.v. Paracetamol (1,000 mg) and i.v. Dimetinden (4 mg) are administered 30–60 minutes prior to the start of infusion. Three hours after the start of FBTA05 infusion, i.v. Paracetamol (500 – 1,000 mg) is repeated. Post-infusion, Paracetamol and Dimetinden are administered, as needed.

In phase I, each patient (cohort A – D) will undergo the same safety part and receive induction doses of FBTA05 on day 0 (10 μg), day 3 (20 μg) and day 7 (50 μg). During the maintenance part, FBTA05 applications are scheduled for course I on day 14 (± 1 day), 21 (± 1 day), 28 (± 1 day) and 35 (± 1 day), for course II on day 42 (± 1 day), 49(± 1 day), 56 (± 1 day) and 63 (± 1 day). Thereby dose escalation of FBTA05 will be performed according to the respective Cohort A – D (Table 1).

Donor lymphocyte infusion is scheduled in each cohort at the end of the safety part (day 7), as well as at the end of course I (day 35) and course II (day 63). The numbers of infused T cells are escalated according to the respective preparative regimen applied for allo-SCT as shown in Table 3. DLI will not be performed in case the of GVHD or active infection at the time of DLI, or in the rare cases that DLI is not available for technical reasons. In this case antibody application will be continued as scheduled without DLI.

**Table 3 T3:** Dose escalation of donor lymphocyte infusions (DLI)

**DLI**	**Haplo-identical SCT**	**HLA-identical SCT**
**d7**	5 ×10^5^ /kg CD3^+^ cells	1 ×10^6^ /kg CD3^+^ cells
**d35**	1 ×10^6^ /kg CD3^+^ cells	5 ×10^6^/kg CD3^+^ cells
**d63**	5 ×10^6^ /kg CD3^+^ cells	1 ×10^7^/kg CD3^+^ cells

*SCT* stem cell transplantation, *HLA* human leukocyte antigen.

In phase II the recommended dose will be applied according to the respective treatment schedule as determined in phase I.

### Study visits

Patients are required to complete screening procedures and 14 treatment visits (11 applications of FBTA05; 3 applications of DLI), so far as the dosage regimen is tolerated according to MTD assessments. Two weeks after the last infusion (week 12), patients will attend an end-of-study visit (EOS). In follow up, patients will attend 4 additional post-study follow-up visits (6, 9, 12 and 24 months after start of treatment). Patients enrolled in phase II will follow the identical screening, treatment and post-study follow-up schedule as for phase I.

### Safety management

An ESB, composed of three independent experienced clinical experts is responsible for the evaluation of the patients. Together with the investigators they decide, whether individual patients may continue the study, and whether or not dose escalation can be applied. The ESB is involved in the assessment and declaration of Serious Adverse Events (SAEs), Suspected Unexpected Serious Adverse Reactions (SUSARs) as well as the evaluation of dose-limiting toxicities (DLT). Moreover, based on the results of the interim analysis at the end of the phase I, the ESB together with the investigators will propose the recommended dose (RD) for phase II.

The condition for a DLT is fulfilled in the case of termination of treatment due to an adverse reaction. Thereby, the treatment schedule for a patient must be terminated if any toxicity grade ≥ 3, condition or adverse event (e.g. body temperature ≥ Grade 3 Common Toxicity Criteria (CTC) (40°C), systolic BP < 75 or > 210 mm Hg, pulse < 50 or > 150 bpm or a dyspnoea grade IV) does not normalize within 3 hours. Furthermore, treatment will be terminated in case of an anaphylactic reaction, including, but not limited to severe angioedema, severe bronchospasm, severe urticaria or anaphylactic shock which occurs during the infusion. An adverse reaction, including clinical conditions of CTC Grade ≥ 3 or clinically relevant laboratory abnormality of CTC Grade ≥ 3 which occurs after the infusion and does not resolve until the planned date of the next infusion will also be grounds for termination of treatment.

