### Primary and secondary endpoints

The primary endpoint in Phase I is the incidence of dose limiting toxicities (DLTs), in phase II the objective response rate. The secondary endpoints are safety and efficacy. Regarding safety, the recommended dose of FBTA05 in combination with DLI for further efficacy studies will be determined. Furthermore, the incidence of adverse events (AEs), the presence of HAMAs after FBTA05 application, the need to discontinue FBTA05 infusion, vital functions, the physical examination findings, laboratory parameters, concomitant medication and as pharmacodynamic endpoints the serum levels of cytokines will be recorded.

In terms of efficacy the clinical benefit rate, the duration of response, the time to progression, the overall survival, the ECOG performance status, the tumor specific response, lymphocyte subsets, activation signs and memory status of T cells will be analysed.

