**Figure 2 F2:**
[figure not shown]
**Treatment schedule.** The FBTA05 treatment schedule consists of three parts: the drug induction part (safety part) and the dose maintenance / escalation parts (course I / II). Thereby the safety part is the same for each study patient, with FBTA05 applications of 10 μg on day 0, 20 μg on day 3 and 50 μg on day 7. FBTA05 dose adjustment for the subsequent treatment courses I and II, will be performed according to the respective cohort A-D (Table 1). Infusion of donor lymphocytes (DLI) will be dose-escalated (Table 3) and applied subsequent to the respective antibody infusions on day 7, day 35 and day 63 of the treatment schedule. The red arrows indicate the application of FBTA05, the green arrows the infusion of donor lymphocytes.

**Table 1 T1:** Dose escalation of FBTA05

**FBT05**	**Day**	**Cohort A**	**Cohort B**	**Cohort C**	**Cohort D**
**Safety part**	**d0**	10 μg	10 μg	10 μg	10 μg
	**d3**	20 μg	20 μg	20 μg	20 μg
	**d7**	50 μg	50 μg	100 μg	200 μg
**FBT05**	**Day**	**Cohort A**	**Cohort B**	**Cohort C**	**Cohort D**
**Course I**	**d14**	50 μg	50 μg	100 μg	200 μg
	**d21**	50 μg	50 μg	100 μg	200 μg
	**d28**	50 μg	50 μg	100 μg	200 μg
	**d35**	50 μg	100 μg	200 μg	300 μg
**Course II**	**d42**	50 μg	100 μg	200 μg	300 μg
	**d49**	50 μg	100 μg	200 μg	300 μg
	**d56**	50 μg	100 μg	200 μg	300 μg
	**d63**	50 μg	100 μg	200 μg	300 μg

FBTA05 (anti-CD3 x anti-CD20 trAb).

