Each cohort includes at least 2 patients. In a strict sequential order, treatment and dose escalation (cohort A-D, Table 1) is performed independently for each disease entity (either CLL / low-grade NHL or high-grade NHL). Thus, treatment of any subsequent patient 2 or 3 at a certain dose level will be started only after the safety part treatment of the previous patient of the same disease entity is completed, and the External Safety Board (ESB), acting as a Dose Steering Board (DSB), agrees to the enrolment of the next patient. The same dose escalation procedure will be applied throughout the study for all Cohorts (A-D). If one dose-limiting toxicity is seen, a total of 3 patients of the same disease entity must be treated at that dose level. If two dose-limiting toxicities are seen at any dose level, treatment for this disease entity is terminated and the MTD will be established at the next lower dosing level. If 2 of 3 patients of the same disease entity in Cohort A show dose-limiting toxicities, the MTD has been reached and lower dose levels may have to be investigated.

After the phase I part of the study an interim analysis will be performed. Based on the outcome of this analysis the recommended dose (RD) for the phase II part will be proposed by the ESB and the investigators on the basis of the MTD and any other relevant safety issues. The recommended dose will not exceed the maximal dose foreseen in the protocol approved by the competent authority. The report of the interim analysis with the recommended dose will be presented to the ethics committee and competent authority. A maximum of 6 patients per disease entity will receive treatment during phase II. If the last Cohort at MTD level in phase I already included 2 or 3 patients for CLL/low grade NHL, respectively high-grade NHL, an additional 4 or 3 patients per disease entity will be enrolled in phase II.

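### The stated DLT condition depends on stopping treatment, so a related grade 3 or higher toxicity first arising after the day-63 infusions is left out of the phase I DLT count and the formal MTD unless the safety board chooses to count it

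*Protocol article*

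**What the plan says.** Primary and secondary endpoints, in the protocol article, makes the DLT the unit of the phase I result: "The primary endpoint in Phase I is the incidence of dose limiting toxicities (DLTs". The same section adds that "the recommended dose of FBTA05 in combination with DLI for further efficacy studies will be determined".

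Safety management says when a DLT exists: "The condition for a DLT is fulfilled in the case of termination of treatment due to an adverse reaction". It then lists three grounds for termination:

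- a grade 3 or higher toxicity that has not normalised within 3 hours, on which the patient's treatment schedule must be ended;
- an anaphylactic reaction during the infusion;
- a reaction or relevant laboratory abnormality of grade 3 or higher "which occurs after the infusion and does not resolve until the planned date of the next infusion will also be grounds for termination".

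Study design gives the rules that use the count: "If one dose-limiting toxicity is seen, a total of 3 patients of the same disease entity must be treated at that dose level", and "If two dose-limiting toxicities are seen at any dose level, treatment for this disease entity is terminated", with the MTD then set at the next lower level.

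Table 1 ends FBTA05 on day 63. The Figure 2 legend says the donor lymphocytes are "applied subsequent to the respective antibody infusions on day 7, day 35 and day 63 of the treatment schedule". Study visits places the end-of-study (EOS) visit two weeks after the last infusion, with follow-up only after that.

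**The concern.** A DLT that exists only through stopping treatment works while treatment is still to come. At the end of the schedule it does not. A serious related reaction that begins after the last antibody infusion and the last DLI cannot lead to termination, so the stated condition cannot be met.

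The place of the gap matters. The day-63 DLI is the largest of the three, and the dose sought is that of FBTA05 combined with DLI. Rationale for performing the study attributes graft-versus-host disease (GVHD) to T lymphocytes in the DLI. Previous trials and clinical data reports one grade 3 case after FBTA05 and DLI among nine compassionate-use patients, without its timing.

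At stake are the phase I primary endpoint and the rule that fixes the MTD. Both rest on two or three patients per dose level and disease entity.

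**Working it through.** **1. The schedule.** FBTA05 infusions: 3 (safety part) + 4 (course I) + 4 (course II) = 11. DLIs: 3. Treatment visits: 11 + 3 = 14, which reproduces the figure in Study visits. Once both day-63 infusions are given, 0 of 11 and 0 of 3 remain.

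**2. Each ground, for a related grade 3 or higher toxicity first arising after both day-63 infusions.**

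| Ground (Safety management) | What it needs | Available after day 63? |
|---|---|---|
| Not normalised within 3 hours | A schedule to terminate | No end date is set, but the schedule is already complete |
| Anaphylactic reaction | An infusion in progress | No |
| Unresolved at the next infusion date | A planned next infusion | No |

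Toxicity during the day-63 antibody infusion, or after any earlier infusion or DLI, can still become a DLT.

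**3. Effect of one uncounted event.** Phase I allows at most 3 patients × 4 cohorts × 2 entities = 24, the stated maximum, so a level holds two or three patients per entity.

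- 1/2 = 50% becomes 0/2 = 0%: the third patient is no longer required.
- 2/3 = 67% becomes 1/3 = 33%: the level is not stopped and the MTD is not set one level lower.

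**4. What bounds the gap.**

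- Time: EOS is day 63 + 14 = day 77, so 14/77 = 18% of the days to EOS are uncovered. This is calendar time, not a share of risk.
- FBTA05: the day-63 dose as a share of the Table 1 total is 50/480 = 10.4% (A), 100/730 = 13.7% (B), 200/1430 = 14.0% (C) and 300/2330 = 12.9% (D). That dose has already been given 8 times in cohort A (days 7 to 56) and 4 times in B to D (days 35 to 56), each time with a next infusion planned.
- DLI (Table 3): day 63 supplies 10/(1 + 5 + 10) = 62.5% of planned CD3+ cells per kg after HLA-identical transplantation and 5/(0.5 + 1 + 5) = 77% after haplo-identical transplantation. The schedule is the same in cohorts A to D.

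**5. Illustration only.** Let p be the probability that a patient has a toxicity of DLT grade, and q the share of those first arising after day 63. The article gives neither, so both are assumed. With two patients, a third after one DLT and a stop at two, P(stop) = p² + 2p²(1 − p). Leaving late events out replaces p by p(1 − q).

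| p | All counted (q = 0) | q = 0.10 | q = 0.25 | q = 0.50 |
|---|---|---|---|---|
| 0.2 | 0.104 | 0.086 | 0.061 | 0.028 |
| 0.3 | 0.216 | 0.179 | 0.129 | 0.061 |
| 0.5 | 0.500 | 0.425 | 0.316 | 0.156 |

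The direction is certain: omission can only lower the chance of stopping. The size depends wholly on p and q.

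**The case against.** **The wording gives a sufficient condition.** Grammatically it does not say that only termination makes a DLT. The ESB evaluates DLTs, and the 3-hour ground has no end date, so the board could count a late event. This stands, and it is why the point is limited to a literal reading. But no other condition is stated, so counting a late event would be a case-by-case choice on the primary endpoint.

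**The article condenses a fuller protocol.** A missing observation window alone would be no finding. Here the article does state the rule and its grounds, and that rule gives the wrong count after the last dose. The full protocol may cover it; this point concerns the article's text.

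**GVHD is a weak example.** The phase I objective is the MTD of FBTA05, GVHD has its own secondary objective, and the DLI schedule is not what differs between cohorts. Under Study treatment, GVHD at a DLI date means withholding the DLI and continuing the antibody. So GVHD as such is not a termination ground, though unresolved GVHD of grade 3 or higher could still meet one. Counting it late should follow that same threshold and no wider one.

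**A reader might infer that late toxicity goes unseen, or that an unsafe dose could reach phase II unchecked.** The article does not support that. Adverse events are recorded. Of the ESB the article says: "Together with the investigators they decide, whether individual patients may continue the study, and whether or not dose escalation can be applied". Study design bases the recommended dose on the MTD and on other relevant safety issues.

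**Conclusion.** The point holds in limited form. Read literally, a related grade 3 or higher toxicity first arising after the day-63 FBTA05 infusion and DLI enters neither the phase I DLT incidence nor the two-DLT rule, unless the ESB decides to count it. The defect is confined to the primary endpoint count and the formal MTD. Escalation decisions and the recommended dose have other safeguards.

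The number of events missed cannot be derived from the document. What can be said is that one such event can change a level's result. The conclusion assumes that the article's DLT condition is the operative one. It is worth fixing before the interim analysis, with medium confidence.

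**What to change.** Keep the existing definition in Safety management and add a sentence to this effect: a related adverse reaction of grade 3 or higher, GVHD included, that arises after the day-63 FBTA05 infusion or DLI and would have met a termination ground had treatment continued, that is, unresolved on day 70 or at the EOS visit (day 77), counts as a DLT although no treatment is left to terminate. Day 70 is 63 + 7, the infusion interval of courses I and II. Resolution by then can be read from adverse event dates at EOS.

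Leave the escalation gate as it is. The stated gate is completion of the previous patient's safety part (day 7) with ESB agreement. Waiting for EOS instead could add about 77 − 7 = 70 days per step, which is not proposed. Finalise DLT status through EOS before the interim analysis sets the MTD.

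Costs:

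- No new visit, but the interim analysis may wait up to about 2 weeks after the last patient's day 63.
- The DLT count may look less favourable.
- A second DLT declared late may lower the MTD after the next level has opened and, under the two-DLT rule, stop treatment of patients of that disease entity already there.
- GVHD starting after EOS stays outside the count and should be reported to the ESB separately.

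### Delayed severe toxicity that starts after the day-63 infusions meets no written DLT condition, so it is left out of the phase I primary endpoint and the MTD rule

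*Protocol article*

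**What the plan says.** Under Primary and secondary endpoints: "The primary endpoint in Phase I is the incidence of dose limiting toxicities (DLTs), in phase II the objective response rate". Under Study design, the rules for adding a third patient, stopping a disease entity and setting the MTD all work on the number of DLTs at a dose level. One DLT requires a total of three patients; two end treatment for that entity and put the MTD one level down.

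Safety management gives the only DLT condition in the article: "The condition for a DLT is fulfilled in the case of termination of treatment due to an adverse reaction". It then lists three grounds for termination:

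- An acute rule: "the treatment schedule for a patient must be terminated if any toxicity grade ≥ 3, condition or adverse event" fails to normalize within 3 hours.
- An anaphylaxis rule, whose examples are "severe angioedema, severe bronchospasm, severe urticaria or anaphylactic shock which occurs during the infusion".
- A rule for grade 3 or higher reactions or relevant laboratory abnormalities "which occurs after the infusion and does not resolve until the planned date of the next infusion will also be grounds for termination" of treatment.

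Study treatment puts the last of the FBTA05 infusions on day 63 and schedules DLI on day 7 "as well as at the end of course I (day 35) and course II (day 63"). Study visits counts 11 FBTA05 and 3 DLI applications, then an end-of-study (EOS) visit two weeks after the last infusion and follow-up at 6, 9, 12 and 24 months. Nothing there links these visits to DLT assessment. The eligibility section adds that a patient with a DLT has to be withdrawn from the study.

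**The concern.** A DLT is tied to ending treatment, and the rule for delayed reactions is tied to a further infusion. After day 63 there is neither. A severe reaction of a kind that would count after day 35 would not count if it began after day 63, although Table 3 gives the largest donor T-cell dose on that day and the rationale section attributes GVHD to the T cells in DLI. The DLT count supplies both the phase I primary endpoint and the MTD. A level could therefore be recorded as free of DLTs while its patients had delayed severe toxicity.

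**Working it through.** **Plan's own figures.** No stated figure depends on this rule; the article gives no DLT rate and no power. The cohort sizes do reproduce: 4 cohorts × 3 patients × 2 entities = 24 in phase I. Adding 2 × (6 − 3 carried over) = 6 gives the stated maximum of 30. A level thus has two or three patients per entity.

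**What each termination rule does once the day-63 infusion and DLI are complete**

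| Rule | What it needs | After day 63 |
|---|---|---|
| Acute, 3 hours | Grade ≥ 3 or listed condition not normalizing; acts by ending the schedule | Not tied to a next infusion, so an acute day-63 reaction may count; no schedule is left to end |
| Anaphylaxis | Examples are described as occurring during the infusion | No further infusion |
| Delayed reaction | Unresolved at the planned next infusion | No such date exists |

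Toxicity during the day-63 infusion, or before that day's DLI, can still end treatment and count. The firm gap is delayed toxicity that starts after both.

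**Exposure on day 63**

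- Donor T cells (Table 3), haplo-identical: 5×10^6 / (0.5 + 1 + 5)×10^6 = 5/6.5 = 76.9% of the planned total. HLA-identical: 10/(1 + 5 + 10) = 62.5%.
- FBTA05 (Table 1), cohorts A to D: 50/480 = 10.4%, 100/730 = 13.7%, 200/1430 = 14.0%, 300/2330 = 12.9%. The day-63 dose equals the doses on days 35 to 56.

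Day 63 is therefore the largest exposure for DLI, but not for the drug being escalated.

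**Illustration 1: late events alone.** Let g be the risk that a patient has a severe delayed event after day 63 (assumed, independent between patients).

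- At least one uncounted event in two patients: 1 − (1 − g)². For g = 0.10, 0.20, 0.30 this is 0.19, 0.36, 0.51.
- Two or more in three patients, which would end the level if counted: 3g²(1 − g) + g³. This is 0.028, 0.104, 0.216.

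**Illustration 2: the stopping rule.** Let p be the full risk of toxicity of dose-limiting type and f the share that arises only after day 63 (both assumed). The rule stops a level with probability S(p) = p² + 2p(1 − p)p. Without late events, p is replaced by p(1 − f).

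| p | All counted | f = 0.25 | f = 0.50 | f = 0.75 |
|---|---|---|---|---|
| 0.20 | 0.104 | 0.061 | 0.028 | 0.007 |
| 0.33 | 0.255 | 0.153 | 0.073 | 0.019 |
| 0.50 | 0.500 | 0.316 | 0.156 | 0.043 |

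For example, at p = 0.33 and f = 0.50: 0.165² × (3 − 2 × 0.165) = 0.0272 × 2.67 = 0.073.

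**The case against.** The case on the other side has real substance.

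- **The 3-hour rule is broad.** It covers any grade 3 or higher toxicity and names no next infusion, so a reader could apply it after day 63. This stands for acute reactions. It does not carry delayed ones: the rule works by ending a schedule that is already complete, and the separate rule allowing a reaction after the infusion until the next planned date would have no purpose if the 3-hour rule governed delayed events too.
- **That a DLT requires termination is inferred.** The wording states when the condition is met, not that nothing else can meet it. The External Safety Board (ESB) evaluates DLTs, and the full protocol may say more. That is fair, but the article gives the board no other criterion, and the point concerns a rule that is stated, not one left out.
- **The MTD is for FBTA05.** DLI doses follow donor match and are the same in every cohort; GVHD is a secondary objective. The rationale section even expects FBTA05 to lower GVHD risk. This limits what can be said about bias in an FBTA05 dose, and the T-cell shares do not measure that bias.
- **Late events are not hidden.** Adverse events are recorded, follow-up runs to 24 months, the ESB and investigators decide on escalation, and the recommended dose may weigh safety matters beyond the MTD. The study is exploratory. All this stands and lowers the severity, but it does not correct the DLT count, the MTD or the primary endpoint.

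**Conclusion.** The point holds for delayed reactions of grade 3 or higher, including severe GVHD, that begin after both day-63 infusions are complete. Followed exactly, the text leaves them out of the phase I primary endpoint and the MTD rule.

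The direction is certain: the omission can only lower the DLT count, so the rule's MTD is the same as, or higher than, it would be with those events counted. The size is not known. The event risks above are assumptions. The only GVHD figure from patients given FBTA05 with DLI is one grade 3 case among the 4 + 4 + 1 = 9 compassionate-use patients, and it was in acute lymphocytic leukemia, which is not among this trial's inclusion diagnoses.

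A reader might infer two stronger statements. One is that no toxicity after the last infusion can ever count; the 3-hour rule leaves room for acute reactions. The other is that the FBTA05 MTD is shown to be too high by an amount reflected in the 62.5 to 77% T-cell shares. That would need late toxicity to depend on the FBTA05 dose, which the documents do not establish, and day 63 carries only about 10 to 14% of the planned FBTA05. This is a should-fix point.

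**What to change.** Reconcile the sections on endpoints, Study design, eligibility and withdrawal, Study visits and Safety management so that:

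1. For phase I counting, a DLT is determined by the plan's own severity and persistence criteria, not by whether any treatment remains to be ended.
2. An observation window after day 63 is stated that ends at the existing EOS visit (day 63 + 14 = day 77), in place of a next-infusion date that does not exist.
3. That window is complete before a level's DLT count and the interim analysis are final.
4. GVHD found at later visits is tabulated by dose level, descriptively and outside the DLT count.
5. A DLT counted after day 63 does not remove the patient from follow-up; the present withdrawal wording would suggest that it does.

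The clinical criteria themselves are for the sponsor and the ESB. The change is not neutral, because DLTs drive stopping and withdrawal and so more events could trigger those rules. No new visits are needed. The cost is protocol wording, a DLT count per level that may close about two weeks later, and an MTD that may come out lower.
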